## **Project summary**

For the first time, a large-scale human intervention study was conducted to unravel the urinary excretion profile and metabolism of the mycotoxin deoxynivalenol (DON) and its modified form deoxynivalenol-3-glucoside (DON-3-glucoside). DON and DON-3-glucoside are common contaminants in cereals and cereal-based food products, and contribute significantly to the dietary intake of mycotoxins. A group of 20 healthy volunteers will be selected for this study. The subjects have to follow a strict cereal-free diet during 3 days. Cereal-based foods and foods containing possible traces of wheat, rye, oats, maize and rice are restricted (*i.e.* bread and bread-based products, breakfast cereals, oat meal, muesli, cereal bars, waffles, cakes, (un)peeled rice, polenta, pizza, tortilla, pasta, popcorn, cereal-based chips, maize, beer, wine, pan meal and sauce-binders). The subjects are asked to detail their daily food intake through a questionnaire. On the third day in the morning, the subjects receive an oral bolus of DON or DON-3-glucoside based on the TDI (1 µg/kg body weight) and their body weight. The volunteers did the study twice: 1) DON administration and 2) DON-3-glucoside administration, between the two mycotoxin administration there are a washout period of two months. In addition, a control group of 4 volunteers follow the same protocol, however do not receive a bolus of DON or DON-3-glucoside after the cereal-free diet. At day 3, volunteers have to collect a urine sample before the administration of the DON or DON-3-glucoside bolus. From the moment of administration, the 24-hours urine sample collection is requested. We deliver to each volunteer 12 containers (1L) to collect the urine.

**Title:** Metabolization and renal excretion of deoxynivalenol and its glucoside.

**Date:** from January to May 2017.

**Protocol identifying number:** NTR6902

**Name sponsor/funder:** Foodball project and Research Foundation Flanders (FWO)

**Address:** FWO, [name]

**Rationale & background information**

**The Rationale specifies the reasons for conducting the research in light of current knowledge. It should include a well documented statement of the need/problem that is the basis of the project, the cause of this problem and its possible solutions. It is the equivalent to the introduction in a research paper and it puts the proposal in context. It should answer the question of why and what: why the research needs to be done and what will be its relevance. The magnitude, frequency, affected geographical areas, ethnic**

**and gender considerations, etc of the problem should be followed by a brief description of the most relevant studies published on the subject.**

Deoxynivalenol (DON), also known as vomitoxin, is a mycotoxin that acts as a potent inhibitor of protein synthesis, stimulates the pro-inflammatory response, cause ribotoxic stress, cytotoxicity and apoptosis, resulting on the impairment of multiple physiological functions, such as the intestinal barrier, growth, immune regulation or reproduction. Furthermore, this mycotoxin has been linked with animal and human gastroenteritis outbreaks due to acute exposition (Pestka, 2010). Despite its toxicity, DON is a highly common mycotoxin in cereals and cereals products (([name], et al., 2012; Marin, Ramos, Cano-Sancho, & Sanchis, 2013) Marin et al., 2013) and as a result it is one of the major mycotoxins in our diets. Thus, exposition studies showed the large exposure of human to this toxin with high percentages of population exceeding the tolerable daily intake (TDI) (Heyndrickx, et al., 2015; Vidal, Cano-Sancho, Marin, Ramos, & Sanchis, 2016).

Furthermore, free mycotoxins, like DON, might not be the only hazard for consumer's health, because the so-called modified mycotoxins are also widely common in food. Modified mycotoxins are toxins attached to more polar functional groups, such as glycosyl residues or sulfates, or to polymeric carbohydrates or protein matrices (Berthiller, Schuhmacher, Adam, & Krska, 2009; Rychlik, et al., 2014). The modified mycotoxins may have plant, fungal, mammalian and food processing origins. A major concern and potential risk for consumers is the possible hydrolysis of modified mycotoxins into their toxic free forms during mammalian digestion (Broekaert, et al., 2015; Grabley, Gareis, Bockers, & Thiem, 1992; V. Nagl, et al., 2014). Contrary to the wealth of information on the free mycotoxins, only limited data are available for mycotoxin derivatives in foods. The co-occurrence of free and modified DON forms has been documented in raw wheat, especially with focus on deoxynivalenol-3-glucoside (DON-3-glucoside), 3-acetyldeoxynivalenol (3-ADON) and 15-acetyldeoxynivalenol (15-ADON). Reported levels of DON-3-glucoside are variable, however, the concentration of DON-3-glucoside can be high and even the same as DON in processed cereals ([name], et al., 2012). 3-ADON and 15-ADON have also been detected in cereals and cereals products with a lower incidence than DON-3-glucoside ([name], et al., 2012). (Berthiller, et al., 2011) demonstrated that several lactic acid bacteria hydrolyse DON-3-glucoside in vitro, which has been a first step to prove the toxicological relevance of DON-3-glucoside. On the other hand, 3-ADON and 15-ADON are rapidly converted to DON during digestion (Broekaert, et al., 2015; Versilovskis, et al., 2012). Thus, due to the high presence of DON conjugates in food and the easy transformation of them to DON, the FAO/WHO Expert Committee (JEFCA) considered DON-3-glucoside to be an additional contributing factor to total dietary exposure to DON (JECFA, 2010).

To know the DON exposition, analysis of urinary levels of DON has been proposed due to its short excretion half-life. However, different studies showed that DON glucuronides, which are the main phase II metabolites of DON, are the most common DON form in urine, specially DON-

3-glucuronide and DON-15-glucuronide (Warth, et al., 2012). So, the analysis of glucuronides forms in urine is crucial for the study of trichothecenes biomarkers, because about 90 % of DON excreted via urine is conjugated with glucuronic acid. For the glucuronides determination, a preliminary approach was developed based on the breakage of deoxynivalenol-glucuronides and subsequent determination of “total deoxynivalenol” (sum of free and released mycotoxins by hydrolysis). Afterwards, a direct method for quantification of glucuronides such as deoxynivalenol-3-glucuronide and deoxynivalenol-15-glucuronide was developed. The analytical developments permitted to find strong correlations between the sum of urinary deoxynivalenol and its glucuronidated metabolites (Turner, White, et al., 2010; Warth, Sulyok, Berthiller, Schuhmacher, & Krska, 2013). These investigations revealed the power of biomarker driven work when compared to traditional exposure assessment by analyzing food stuff. However, the analysis of DON in urine presents some uncertainties and limitation to fully validate the DON excretion metabolism and renal excretion. Firstly, biomonitoring data may depend on the moment in time when the sample is collected (Clewell, Tan, Campbell, & Andersen, 2008). Furthermore, there is a lack of information in the absorption and excretion rate of it. Finally, the high presence of DON conjugates in food like DON-3-glucoside or acetyl-deoxynivalenol (ADONs) add more uncertainties for the correlation between urinary DON and DON intake.

### **Study goals and objectives**

**Goals are broad statements of what the proposal hopes to accomplish. They create a setting for the proposal. Specific objectives are statements of the research question(s). Objectives should be simple (not complex), specific (not vague), and stated in advance (not after the research is done). After statement of the primary objective, secondary objectives may be mentioned.**

Due to the lack of information about DON absorption and excretion, the aims of this study are the description of the DON and metabolites excretions patterns and know the absorption and excretion rates of it. Moreover, the results can be useful to build an standardized method to estimate deoxynivalenol-intake by means of biomarkers.

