### **Study Design**

**The scientific integrity of the study and the credibility of the study data depend substantially on the study design and methodology. The design of the study should include information on the type of study, the research population or the sampling frame, and who can take part (e.g. inclusion and exclusion criteria, withdrawal criteria etc.), and the expected duration of the study**

**(The same study can be described in several ways, and as complete a description of the study as possible should be provided. For example, a study may be described as being a basic science research, epidemiologic or social science research, it may also be described as observational or interventional; if observational, it may be either descriptive**

**or analytic, if analytic it could either be cross-sectional or longitudinal etc. If experimental, it may be described as a controlled or a non controlled study. The link below provides more information on how to describe a research study**

The human controlled intervention study is conducted according to the guidelines laid down in the declaration of Helsinki, and was approved by the Ethical Committee of the Ghent University Hospital (B670201630414). Participants, members of the research group and familiars, are contacted providing an invitation letter and can register for the study within two weeks after the call. All participants have to sign an informed consent. Each participant is informed on his/her right to withdraw from the study at any time and to consult a doctor immediately and inform us if they fell not right during the study but no adverse event are reported for any volunteers. Besides, no medical examinations or interventions are carried out in this study. The study is performed with 20 volunteers throughout an intervention and longitudinal trail, and recruited in Flanders (Belgium). All people older than 18 years old can take part in the study, less pregnant or breast-feeding women due to the potential risk to both mother and foetuses and persons with severe problems with liver, bile or kidney due to related risks for interferences with the mycotoxin metabolism. The volunteers are instructed to file a socio-demographic questionnaire involving details on age, gender, length, body weight, smoking, diseases, drugs or supplements, pregnancy, breast-feeding, diet and daily coffee consumption.

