The subjects have to follow a strict cereal-free diet during 3 days (Figure 1). Cereal-based foods and foods containing possible traces of wheat, rye, oats, maize and rice are restricted (*i.e.* bread and bread-based products, breakfast cereals, oat meal, muesli, cereal bars, waffles, cakes, (un)pealed rice, polenta, pizza, tortilla, pasta, popcorn, cereal-based chips, maize, beer, wine, pan meal and sauce-binders). The subjects are asked to detail their daily food intake through a questionnaire. On the third day in the morning, the subjects receive an oral bolus of DON or DON-3-glucoside based on the TDI ( $1\text{ }\mu\text{g/kg}$  body weight) and their body weight. The volunteers did the study twice: 1) DON administration and 2) DON-3-glucoside administration, between the two mycotoxin administration there are a washout period of two months. In addition, a control group of 4 volunteers follow the same protocol, however do not receive a bolus of DON or DON-3-glucoside after the cereal-free diet.

At day 3, volunteers have to collect a urine sample before the administration of the DON or DON-3-glucoside bolus (Figure 1). From the moment of administration, the 24-hours urine sample collection is requested. We deliver to each volunteer 12 containers (1L) to collect the urine. For every sampling point, time (hour of urine collection) and voided volume is recorded. All samples will be individually aliquotted to 20 mL, and stored in the freezer at  $-20^{\circ}\text{C}$  upon analysis. The samples are analysed with a Waters Acquity UPLC system coupled to a Quattro XEVO TQS mass spectrometer (Waters, Manchester, UK) was used to analyse the urine samples. Data acquisition and processing is performed with MassLynx™ version 4.1 and

QuanLynx® version 4.1 software (Waters, Manchester, UK). A Waters Acquity UPLC® HSS T3 (2.1 x 100 mm, 1.8 µm) column is applied (Waters, Manchester, UK).

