### **Data Management and Statistical Analysis**

**The protocol should provide information on how the data will be managed, including data handling and coding for computer analysis, monitoring and verification. The statistical methods proposed to be used for the analysis of data should be clearly outlined, including reasons for the sample size selected, power of the study, level of significance to be used, procedures for accounting for any missing or spurious data etc. For projects involving qualitative approaches, specify in sufficient detail how the data will be analysed.**

Firstly, we agree a coding system for the samples. The coding system is that all samples have two number separated by a "." where the first number is the volunteer id and the second number is the number of the sample of each volunteer. So the first urine sample of the volunteer 1 is 1.1 and the second sample of the volunteer 1 was 1.2. On the other hand, the second sample for the volunteer 2 is 2.1 and the second samples of the volunteer 2 is 2.2. We introduce an excel file all the information for each volunteer id.

Once we analyse the samples, the data of each sample is introduced in the same excel file and the results of each mycotoxin are introduced separately. Then, all obtained results are carried out on molar basis taking the molecular weight of the analytes (DON, 296 g/mole; DON-3-glucoside, 458 g/mole; DON-3-glucuronide and DON-15-glucuronide, 472 g/mole; DOM-1, 280 g/mole; 3-ADON and 15-ADON, 338 g/mole) and the total volume of each sampling point into account. Associations between independent and dependent variables are assessed by using univariate and multivariable linear regression models. Independent variables include age (years), gender, body mass index (BMI),

and the consumption of coffee. The statistical analysis is performed using the software Microsoft Excel® 2010 and SPSS® 15.0.

The excretion profiles are based in values obtained each hour after the bolus administration from a varying number of volunteers per time period. For instance, results from 61 to 120 minutes are clustered in the second hour.

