### **Expected Outcomes of the Study**

**The protocol should indicate how the study will contribute to advancement of knowledge, how the results will be utilized, not only in publications but also how they will likely affect health care, health systems, or health policies.**

The results will be published in a scientific journal and presented in international conferences. The expected outcomes should help to provide a better knowledge in the toxicokinetics of DON and DON-3-glucoside and its renal excretion in humans. Furthermore, results will also give information about which is the best method to analyse DON exposure through the urine. The results will give information about DON biomarkers, excretion rate and speed of excretion to know if it is better to collect only the morning urine or 24 h urine collection.

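### The protocol sets out to learn DON's absorption rate, but 24 hours of urine after an oral dose cannot identify it without an outside assumption or external data

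*Protocol*

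**What the plan says.** Study goals and objectives names two things to be learned about DON: its excretion patterns, and to "know the absorption and excretion rates of it". Rationale & background information gives the same gap as a reason for the study: "there is a lack of information in the absorption and excretion rate of it".

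Study Design describes what is done. On day 3 "the subjects receive an oral bolus of DON or DON-3-glucoside based on the TDI". Before that, "volunteers have to collect a urine sample before the administration of the DON or DON-3-glucoside bolus". Afterwards, "From the moment of administration, the 24-hours urine sample collection is requested". The same section says that "no medical examinations or interventions are carried out in this study". Methodology and the volunteers' urine collection instructions also describe urine only.

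Data Management and Statistical Analysis converts the measured analytes to moles: DON, DON-3-glucoside, the two DON glucuronides, and "DOM-1, 280 g/mole; 3-ADON and 15-ADON, 338 g/mole". It multiplies by voided volume, groups results by hour after the bolus, and fits linear regressions on age, gender, BMI and coffee. No kinetic model is stated.

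Expected Outcomes of the Study promises to "provide a better knowledge in the toxicokinetics of DON and DON-3-glucoside and its renal excretion in humans".

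**The concern.** Absorption is a named objective, yet nothing in the design observes it. Urine shows what has been absorbed and then excreted by the kidney in a form that the assay measures. A dose that was absorbed but left by another route, or as an unmeasured product, looks the same as a dose that was never absorbed.

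At stake is what the trial may conclude. Each volunteer is to receive both DON and DON-3-glucoside, and the rationale treats DON-3-glucoside as a contributor to total DON exposure. If urinary recovery is lower after DON-3-glucoside, it matters whether this may be called lower absorption. The aim as worded invites that step and nothing in the protocol guards against it.

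**Working it through.** The protocol gives no figure on this point, so there is nothing to reproduce. The check asks whether the planned data can identify the quantity named in the aim.

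**Inputs from the protocol:** oral dosing, urine for 24 h, seven measured analytes in moles, no other specimen, no kinetic model.

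**Assumptions, not in the protocol:** linear first-order absorption and one-compartment disposition; every numerical value of the fractions, rate constants and half-lives below; complete urine collection; measured analytes that come from the dose.

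**Model.** Let F be the fraction absorbed, fe the fraction of the absorbed dose excreted in urine as the measured analytes, ka the absorption rate constant and k the elimination rate constant. The cumulative amount in urine, as a share of the dose, is

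U(t) = F × fe × [1 − (ka·e^(−kt) − k·e^(−ka·t)) / (ka − k)].

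**Reading 1: rate as extent.** As t grows, U(t) tends to R = F × fe. Only the product is observed. Since fe cannot exceed 1, F lies between R and 1:

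| Recovery R | Range of F that fits | F if fe = 0.9 | F if fe = 0.7 |
|---|---|---|---|
| 40% | 40% to 100% | 44% | 57% |
| 50% | 50% to 100% | 56% | 71% |
| 60% | 60% to 100% | 67% (0.6/0.9) | 86% (0.6/0.7) |
| 63% | 63% to 100% | 70% | 90% |
| 80% | 80% to 100% | 89% | not possible (0.8/0.7 > 1) |

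The time course does not help. With ka = 1.5/h and k = 0.25/h, the pairs (F, fe) = (0.9, 0.7) and (0.7, 0.9) give the same curve at all 24 hourly points (maximum difference 0.0).

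The comparison of toxins has the same limit. Recoveries of 63% and 40% are both compatible with F = 0.9, with fe = 0.63/0.9 = 0.70 in one case and 0.40/0.9 = 0.44 in the other.

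**Reading 2: rate as speed.** Exchanging ka and k changes the sign of both numerator and denominator in the fraction, so U(t) is unchanged. With F × fe = 0.63, ka = 1.5/h and k = 0.25/h (half-lives 0.46 h and 2.77 h):

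- at 4 h: 0.63 × [1 − (1.5·e^(−1) − 0.25·e^(−6))/1.25] = 0.63 × (1 − 0.441) = 35.2%;
- at 24 h: 0.63 × [1 − 1.5·e^(−6)/1.25] = 0.63 × 0.997 = 62.8% (the second exponential is negligible).

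With ka = 0.25/h and k = 1.5/h the values are the same, and the maximum difference over the 24 hourly points is 0.0. In a model that measures DON and its glucuronide separately in urine, the exchange still leaves both curves unchanged (differences of 2e-14 and 3e-13, which is numerical error). So the urine data give a pair of rate constants without labels.

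**The case against.** **The exchange of rate constants depends on an assumed model.** This stands. It is exact for linear one-compartment first-order kinetics, which the protocol does not specify. Even there only the labels are open, and assuming that absorption is the faster step would settle them. A statistical analysis plan, not at hand, could state that. It would not separate F from fe, however, and no analysis plan can supply a specimen or a reference route that was not part of the design.

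**The word rate is ambiguous.** Expected Outcomes lists excretion rate and speed of excretion separately, which suggests that rate means extent. That is a fair reading, and under it the first result applies in full. The aim is not identified under either reading.

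**The scope is narrow.** The study title and summary concern metabolism and urinary excretion. Absorption appears as an aim in one sentence, with its motivation in the rationale. This stands and limits the weight of the point.

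Two stronger inferences are tempting, and the documents do not support them. A reader might infer that the study will report recovery as absorption; no section says so. A reader might also infer that urine says nothing about the speed of absorption. It does carry information: with an assumed elimination half-life of 3 h, absorption half-lives of 0.25 h and 1 h give 45.5% versus 31.3% of the eventual urinary amount excreted by 3 h, 56.7% versus 43.6% by 4 h, and 72.7% versus 63.3% by 6 h. The contrast is spread over many voids. What is missing is the label, not the signal.

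**Conclusion.** The point holds in limited form. The protocol states an aim on absorption that its own data cannot deliver.

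On extent, recovery is a lower bound on the fraction absorbed, and the width of the uncertainty is everything from the observed recovery up to 100%. This needs no compartmental model; it rests on complete collection and on the measured analytes coming from the dose. On speed, the result rests on the assumed linear one-compartment model and on the absence of any stated assumption about which step is faster.

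The statement is about these data alone. External plasma or intravenous data, or an explicit assumption, could identify more, but the protocol names none. The excretion pattern, the urinary excretion rate and the biomarker aims are untouched. The point is worth correcting because it changes what may be concluded from a recovery difference between the two toxins.

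**What to change.** Restate the aim in Study goals and objectives as two quantities for each toxin: the urinary excretion rate per collection interval, and the cumulative 0–24 h urinary recovery of DON plus measured metabolites as a percentage of the molar dose. Either drop the absorption rate, or state the assumption or external data that would identify it and say whether extent or speed is meant.

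Add to Data Management and Statistical Analysis, and reflect in Expected Outcomes, that recovery is a lower bound on the fraction absorbed, and that a difference in recovery between DON and DON-3-glucoside is not by itself a difference in absorption.

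This costs a rewording and a narrower claim. It needs no new samples or volunteers, which suits a study whose Duration of the Project section already reports sampling as finished.

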### **Study Design**

**The scientific integrity of the study and the credibility of the study data depend substantially on the study design and methodology. The design of the study should include information on the type of study, the research population or the sampling frame, and who can take part (e.g. inclusion and exclusion criteria, withdrawal criteria etc.), and the expected duration of the study**

**(The same study can be described in several ways, and as complete a description of the study as possible should be provided. For example, a study may be described as being a basic science research, epidemiologic or social science research, it may also be described as observational or interventional; if observational, it may be either descriptive**

**or analytic, if analytic it could either be cross-sectional or longitudinal etc. If experimental, it may be described as a controlled or a non controlled study. The link below provides more information on how to describe a research study**

The human controlled intervention study is conducted according to the guidelines laid down in the declaration of Helsinki, and was approved by the Ethical Committee of the Ghent University Hospital (B670201630414). Participants, members of the research group and familiars, are contacted providing an invitation letter and can register for the study within two weeks after the call. All participants have to sign an informed consent. Each participant is informed on his/her right to withdraw from the study at any time and to consult a doctor immediately and inform us if they fell not right during the study but no adverse event are reported for any volunteers. Besides, no medical examinations or interventions are carried out in this study. The study is performed with 20 volunteers throughout an intervention and longitudinal trail, and recruited in Flanders (Belgium). All people older than 18 years old can take part in the study, less pregnant or breast-feeding women due to the potential risk to both mother and foetuses and persons with severe problems with liver, bile or kidney due to related risks for interferences with the mycotoxin metabolism. The volunteers are instructed to file a socio-demographic questionnaire involving details on age, gender, length, body weight, smoking, diseases, drugs or supplements, pregnancy, breast-feeding, diet and daily coffee consumption.

The subjects have to follow a strict cereal-free diet during 3 days (Figure 1). Cereal-based foods and foods containing possible traces of wheat, rye, oats, maize and rice are restricted (*i.e.* bread and bread-based products, breakfast cereals, oat meal, muesli, cereal bars, waffles, cakes, (un)pealed rice, polenta, pizza, tortilla, pasta, popcorn, cereal-based chips, maize, beer, wine, pan meal and sauce-binders). The subjects are asked to detail their daily food intake through a questionnaire. On the third day in the morning, the subjects receive an oral bolus of DON or DON-3-glucoside based on the TDI ( $1\text{ }\mu\text{g/kg}$  body weight) and their body weight. The volunteers did the study twice: 1) DON administration and 2) DON-3-glucoside administration, between the two mycotoxin administration there are a washout period of two months. In addition, a control group of 4 volunteers follow the same protocol, however do not receive a bolus of DON or DON-3-glucoside after the cereal-free diet.

At day 3, volunteers have to collect a urine sample before the administration of the DON or DON-3-glucoside bolus (Figure 1). From the moment of administration, the 24-hours urine sample collection is requested. We deliver to each volunteer 12 containers (1L) to collect the urine. For every sampling point, time (hour of urine collection) and voided volume is recorded. All samples will be individually aliquotted to 20 mL, and stored in the freezer at  $-20^{\circ}\text{C}$  upon analysis. The samples are analysed with a Waters Acquity UPLC system coupled to a Quattro XEVO TQS mass spectrometer (Waters, Manchester, UK) was used to analyse the urine samples. Data acquisition and processing is performed with MassLynx™ version 4.1 and

QuanLynx® version 4.1 software (Waters, Manchester, UK). A Waters Acquity UPLC® HSS T3 (2.1 x 100 mm, 1.8 µm) column is applied (Waters, Manchester, UK).

The results are submitted an statistical analysis. Firstly, all obtained results are carried out on molar basis taking the molecular weight of the analytes (DON, 296 g/mole; DON-3-glucoside, 458 g/mole; DON-3-glucuronide and DON-15-glucuronide, 472 g/mole; DOM-1, 280 g/mole; 3-ADON and 15-ADON, 338 g/mole) and the total volume of each sampling point into account. Associations between independent and dependent variables are assessed by using univariate and multivariable linear regression models. Independent variables included age (years), gender, body mass index (BMI), and the consumption of coffee. The statistical analysis was performed using the software Microsoft Excel® 2010 and SPSS® 15.0.

**Figure 1.** Scheme of the study design.

[figure not shown]

